## Abstract

**Background:**

Early neurological deterioration (END) remains challenging despite guideline-based treatments in patients with acute ischemic stroke (AIS). To date, limited evidence has been established to prevent END. Therefore, this study aims to determine whether Qingre Huatan Formula (QHF) initiated within 48 h of stroke onset prevents END in AIS patients compared with placebo.

**Methods:**

The Qingre Huatan Formula for the Prevention of Early Neurological Deterioration in Acute Ischemic Stroke (QUIET) trial is a randomized, placebo-controlled, double-blind, parallel-group pilot study. Seventy-two eligible patients with AIS within 48 h of symptom onset will be randomly (1:1) assigned to receive either QHF or placebo treatment for 10 days and will subsequently be followed up to 90-days. The primary outcome is the proportion of END within 7 days of stroke onset, defined as a National Institutes of Health Stroke Scale (NIHSS) score increase of ≥2 points. Secondary outcomes mainly include the change in NIHSS score from baseline to 10 days after randomization, and the proportion of patients achieving a good functional outcome (modified Rankin Scale score ≤ 2).

**Discussion:**

This trial will provide valuable evidence for the efficacy and safety of traditional Chinese medicine for END in AIS patients.

**Clinical trial registration:**

https://register.clinicaltrials.gov, identifier NCT06857487 (registered on February 27, 2025).

## Introduction

Stroke is a major global health threat, imposing a substantial burden on individuals and public health systems (1, 2). Ischemic stroke constitutes roughly two-thirds of all new stroke events worldwide (3). Acute ischemic stroke (AIS) is marked by abrupt neurological deficit onset and rapid clinical progression, often culminating in severe disability. Despite guideline-based usual care, however, 5%−40% of patients develop early neurological deterioration (END) within hours or days of symptom onset (4), which is associated with poor clinical outcomes and increased mortality (4–7).

END is one of the most significant challenges in AIS management. Currently, its clinical handling faces three core dilemmas: First, its pathogenesis involves multiple pathophysiological pathways that are intrinsically complex and accompanied by numerous risk factors (8). Second, validated early prediction tools are lacking, impeding rapid identification of high-risk END patients shortly after onset and thereby delaying intensified monitoring and individualized intervention. Moreover, current reperfusion, antithrombotic and neuroprotective strategies show limited efficacy specifically targeting END (9). As a result, the development of safe and effective therapies for this condition has become an urgent unmet need in the acute management of ischemic stroke.

Traditional Chinese medicine (TCM) has accumulated substantial experience in syndrome differentiation and proven herbal formulas for the prevention and treatment of AIS. High-quality clinical evidence has recently emerged, with studies published in leading international journals, underscoring TCM's pivotal role in this field and its encouraging prospects for curbing END (10–12). Our previous work identified phlegm-heat syndrome as a core pattern in the acute stage of ischemic stroke (13). Moreover, the persistence of phlegm-heat syndrome slows neurological recovery and increases the risk of END (14). These findings indicate that prompt administration of heat-clearing and phlegm-resolving therapy is critical for resolving phlegm-heat syndrome, thereby promoting neurological recovery and preventing END. Accordingly, we developed the Qingre Huatan Formula (QHF), a traditional Chinese medicine formula designed specifically for clearing heat and resolving phlegm in AIS patients. Therefore, we designed a randomized, placebo-controlled, double-blind, parallel-group pilot study to demonstrate the efficacy and safety of QHF for the prevention of END in AIS patients.

## Methods

### Study design

The Qingre Huatan Formula for the prevention of early neurological deterioration in acute ischemic stroke (QUIET) trial is a randomized, placebo-controlled, double-blind, parallel-group pilot study registered with ClinicalTrials.gov (NCT06857487) prior to patient enrollment. The primary objective of this study is to assess the effectiveness and safety of QHF vs. placebo for AIS patients at high risk of END. We hypothesize that QHF will be superior to placebo at reducing the risk of END within 7 days of stroke onset, defined as a National Institutes of Health Stroke Scale (NIHSS) score increase of ≥2 points. Furthermore, we will explore the neuroimaging, biological indicators and other dimensions of patients suffering from the phlegm-heat syndrome in AIS. This trial protocol was approved by the institutional review board of Dongzhimen Hospital, Beijing University of Chinese Medicine, Beijing, China (No. 2023DZMEC-410-02). The protocol design is based on the Standard Protocol Items: Recommendations for Interventional Trials (SPIRIT) guidelines (15). The SPIRIT checklist is shown in the Supplementary material.

### Recruitment of participants

This study will recruit 72 patients diagnosed with AIS. Open recruitment for AIS patients will be performed both in Dongzhimen Hospital of Beijing University of Chinese Medicine (Beijing, China) and Fangshan Hospital of Beijing University of Chinese Medicine (Beijing, China). Recruitment advertisements will be displayed online and on hospital notice boards, allowing patients to voluntarily contact investigators. Potential patients will be screened for eligibility based on the inclusion and exclusion criteria. Eligible patients will be informed of the risks and benefits of the study. If they agree to participate in the study, patients and/or their representatives will sign the informed consent form. Patient enrollment will begin in December 2025 and end in October 2026. The schematic diagram of the patient timeline is presented in Figure 1.

**Figure 1 F1:**
[figure not shown]
The diagram of the QUIET trial.

### Patient selection

This study will enroll patients aged 18–80 years who are diagnosed with AIS within 48 h of symptom onset and have a total score ≥10 for both TCM phlegm-dampness and internal-fire syndrome elements, as assessed by the Ischemic Stroke TCM Syndrome Diagnostic Scale (ISDS). The ISDS is a validated instrument developed by our research team (16); the full scale and detailed scoring rules are provided in the Supplementary material. Syndrome differentiation will be performed by at least two attending physicians or higher who have received standardized training on the ISDS. In cases of disagreement, a third senior expert will be consulted to reach a consensus. Inter-rater reliability will be assessed using the Kappa statistic based on 20 pilot cases, with a target Kappa value ≥0.80 indicating good consistency. Regular quality control meetings will be held throughout the trial to ensure consistency in syndrome differentiation.

Patients must also meet the criteria for being at high risk of END, defined as either: (1) MRI showing new ischemic lesions with a DWI-ASPECTS score ≤ 7; or (2) at least two of the following clinically established risk factors for END: hypertension, diabetes mellitus, atrial fibrillation, hyperglycemia at admission, baseline NIHSS score, large vessel occlusion (internal carotid artery or middle cerebral artery M1 segment), or elevated peripheral inflammatory markers. These criteria are based on current evidence and guidelines for END prediction (5, 17–19). The detailed inclusion and exclusion criteria are provided in Table 1.

**Table 1 T1:** Inclusion and exclusion of the QUIET trial.

Inclusion criteria
1. Inpatients diagnosed with AIS.
2. Patients diagnosed with phlegm-heat syndrome based on the Ischemic Stroke TCM Syndrome Diagnostic Scale (ISDS).
3. Patients at high risk of END, defined as either: (1) MRI showing new ischemic lesions with a DWI-ASPECTS score ≤ 7; or (2) at least two of the following clinically established risk factors for END: hypertension, diabetes mellitus, atrial fibrillation, hyperglycemia at admission, baseline NIHSS score, large vessel occlusion (internal carotid artery or middle cerebral artery M1 segment), or elevated peripheral inflammatory markers.
4. Acute ischemic stroke within 48 hours after symptom onset (interval from symptom onset to eligibility screening and enrollment)
5. Aged 18–80 years, male or female.
6. The patient or their legal representative has signed the informed consent form.
15.6-7.4,13.3499pt**Exclusion criteria**
1. Suspected secondary stroke induced by brain tumor, traumatic brain injury, or hematological disorders.
2. Dependent on activities of daily living before the present acute stroke (defined as pre-stroke mRS score ≥ 2).
3. Motor dysfunction caused by other severe diseases (e.g., severe osteoarthritis).
4. Known severe liver dysfunction (ALT/AST > 2 × ULN).
5. Known severe kidney dysfunction (serum creatinine > 1.5 × ULN).
6. Known severe aphasia or mental illness affecting clinical information collection and evaluation.
7. Known hypersensitivity to any component of Qingre Huatan Formula or Chinese herbal medicines with the same efficacy.
8. Pregnancy, potential pregnancy or breastfeeding.
9. Currently participating in other interventional clinical trials.

AIS, acute ischemic stroke; ALT, alanine aminotransferase; ASPECTS, Alberta Stroke Program Early CT Score; AST, aspartate transaminase; DWI, diffusion weighted imaging; END, early neurological deterioration; MRI, magnetic resonance imaging; mRS, Modified Rankin Scale; TCM, traditional Chinese medicine; ULN, upper limit of normal value.

### Randomization, allocation, and blinding

Eligible patients will be randomly assigned (1:1) to the intervention or control group using permuted block randomization with a block size of 4, stratified by centre. The allocation sequence, generated and kept under confidential seal by an independent biostatistician using the SAS 9.4 PROCPLAN, will simultaneously serve as the drug-code list for labeling the identical packages of trial medication and matched placebo.

To maintain blinding, QHF and placebo granules are identical in appearance, taste, smell, and weight, and are produced by New Green Pharmaceutical Co., Ltd. All investigators, patients, statisticians, and outcome assessors will remain blinded to group assignment throughout the trial until the blind codes are unlocked. All adverse events will be reported using standardized terminology without revealing group assignment, and concomitant medications with potential unblinding effects (e.g., TCM treatments with similar efficacy) are strictly prohibited. Regular monitoring will assess blinding integrity, with any breaches documented and reported.

Emergency unblinding will be permitted only for serious adverse events (SAEs) where knowledge of treatment assignment is essential for patient management. Requests must be approved by the principal investigator or an independent Data Safety Monitoring Board (DSMB) member and executed via a secure web-based system or sealed envelope. All unblinding events will be documented, and affected participants will be excluded from per-protocol analyses while others remain blinded.

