#### Safety outcomes

Safety will be monitored continuously throughout the trial, capturing all adverse events (AEs), treatment-emergent adverse events (TEAEs), SAEs, and clinically relevant changes in vital signs, physical examination, ECG, and standard laboratory parameters.

An adverse event (AE) is defined as any untoward medical occurrence that emerges or worsens during the study period, from informed consent through final follow-up. AEs will be graded according to the common terminology criteria for adverse events (CTCAE) Version 5.0 as mild (grade 1), moderate (grade 2), severe (grade 3), life-threatening (grade 4), or fatal (grade 5). treatment-emergent adverse events (TEAEs) are AEs that occur or worsen following the first dose of study medication.

Serious adverse events (SAEs) are defined as any AE that,s regardless of dose or causality: (1) results in death; (2) is life-threatening; (3) requires inpatient hospitalization or prolongation of existing hospitalization; (4) results in persistent or significant disability or incapacity; (5) is a congenital anomaly or birth defect; or (6) requires intervention to prevent permanent impairment or damage.

At each study visit, participants will be systematically questioned about any AEs using non-leading questions. All AEs, regardless of severity or causality, will be recorded in CRFs with detailed information including onset date, duration, severity, relationship to study drug, actions taken, and outcome. The relationship between the AE and the study drug will be assessed by the site investigator using a five-category scale: definitely related, probably related, possibly related, probably unrelated, or definitely unrelated. All AEs will be managed according to standard clinical practice, with appropriate treatment provided as necessary.

All SAEs must be reported to the principal investigator within 24 h of awareness. The principal investigator will then report the SAEs to the institutional review board (IRB) and the DSMB within the required timeframe (typically within 7 calendar days for fatal or life-threatening events, and within 15 calendar days for other SAEs). All SAEs will be followed until resolution or stabilization.

The overall schedule of trial-related activities and data collection is presented in Table 2.

**Table 2 T2:** Schedule of the study process.

Time point	Treatment period					Follow-up period	
	Baseline (Day 1)	Day 3	Day 5	Day 7	Day 10 or discharge	Day 30	Day 90

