Rooted in thousands of years of continuous development, TCM has accumulated systematic experience in preventing and treating AIS, and it has fostered a number of well-established drugs with verified efficacy. During the past decade, research in this area has accelerated, generating a succession of high-quality clinical evidence that supplies new therapeutic options for this condition (10–12). Our earlier research highlighted the phlegm-heat syndrome as a key pattern in AIS (13). Timely heat-clearing and phlegm-resolving therapy is essential for symptom resolution, neurological recovery, and END prevention (14, 27). Accordingly, we developed the Qingre Huatan Formula (QHF), comprising Gastrodiae Rhizoma, Salviae Miltiorrhizae Radix et Rhizoma, Trichosanthis Fructus, Arisaema cum Bile, Rhei Radix et Rhizoma, Gardeniae Fructus and Acori Tatarinowii Rhizoma. According to traditional Chinese medicine theory, these herbs act synergistically to extinguish wind-phlegm, clear heat and purge the bowels, and open the orifices to unblock collateral circulation.

This study has several strengths in the field of preventing END in AIS. First, we pioneered the use of a RCT design to systematically evaluate the efficacy and safety of traditional Chinese medicine interventions for END. Second, by enrolling only confirmed high-risk END patients, we enhanced the precision of the estimates and statistical power.

We acknowledge that the optimal definition of END remains debated, with no universally accepted threshold, as highlighted in a systematic review (4). While some studies have used a ≥4-point NIHSS increase as the threshold for clinically meaningful deterioration, recent randomized trials published in JAMA Neurology (25, 28) have successfully employed the ≥ 2-point definition as a primary or key secondary endpoint, demonstrating its ability to capture clinically significant treatment effects. Evidence from cohort studies further suggests that a ≥2-point increase is a sensitive predictor of poor outcomes and in-hospital mortality, and this threshold may be particularly appropriate for identifying early deterioration in high-risk populations where timely intervention is critical (29, 30). Future larger trials may consider sensitivity analyses using different END thresholds to further inform this methodological question.

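### A fixed, published block of 4 whose sequence is also the drug-code list shifts the odds on block-mates' arms after an emergency unblinding, so the design does not fully secure that others remain blinded

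*Protocol article*

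**What the plan says.** All core statements are in the protocol article under Randomization, allocation, and blinding.

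- Allocation is 1:1, "using permuted block randomization with a block size of 4, stratified by centre". One block size is given, and it is published.
- The sequence is "generated and kept under confidential seal by an independent biostatistician", and it "will simultaneously serve as the drug-code list for labeling the identical packages of trial medication and matched placebo".
- Emergency unblinding is limited to serious adverse events in which the arm is essential to managing the patient. It needs approval and is documented. Afterwards "affected participants will be excluded from per-protocol analyses while others remain blinded".
- Blinding integrity is to be monitored, and breaches reported.

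Four other places bear on a secondary point.

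- The Discussion describes the formula, in terms of traditional Chinese medicine theory, as acting to "clear heat and purge the bowels".
- Treatment names caramel, picrin and burnt grain buds as the main placebo ingredients.
- Safety outcomes says: "At each study visit, participants will be systematically questioned about any AEs using non-leading questions". Table 2 marks adverse events and NIHSS on the same in-hospital days, including Days 3, 5 and 7.
- Follow up procedures says that the NIHSS assessors are trained, blinded and subject to a 10% audit.

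**The concern.** A block of 4 at 1:1 always holds two patients on each arm. Once one member's arm is known, the other three are no longer evenly balanced between the arms, and sealing the list does not change that. Nobody needs to see the list: the block size is public and centre is the only stratum. If patients are allocated in list order, a site's own enrolment order (1 to 4, 5 to 8, and so on) shows who shares a block. If pack numbers also follow the sequence, they give a second route.

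This matters because the primary outcome is a rater-scored rise of only 2 NIHSS points within 7 days of onset (Efficacy outcomes), and the site investigator judges whether an adverse event is related to the drug (Safety outcomes). Partial knowledge of the arm could colour either judgement.

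**Working it through.** **Consistency of the stated figures.** 2 × 36 = 72 = 18 × 4, so the target fills 18 complete blocks if each centre's total is a multiple of 4. The article states no figure for the leak, so there is none to reproduce.

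**Step 1: one block, membership known.** There are 6 equally likely sequences of two A and two B.

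- One reveal (say A): the three remaining places hold one A and two B. P(a given block-mate is in the opposite arm) = 2/3, up from 1/2. Nobody is determined.
- Two reveals: P(same arm) = 1/3, and the other two are then certain. P(opposite arms) = 2/3, and the other two are one A and one B, back to 50:50.
- Three reveals: the fourth is certain.

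**Step 2: the whole trial.** The article gives no unblinding rate, so the rate u is an assumption, taken as independent across patients.

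- Expected number unblinded: 72u.
- Patients not unblinded who have at least one revealed block-mate: 72(1 − u)[1 − (1 − u)³].
- P(a given block is determined): d = 6u²(1 − u)² × 1/3 + 4u³(1 − u) + u⁴. P(at least one of 18 blocks) = 1 − (1 − d)¹⁸.

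| u (assumed) | Unblinded | With a revealed block-mate | P(some block determined) |
|---|---|---|---|
| 1% | 0.7 | 2.1 | 0.4% |
| 3% | 2.2 | 6.1 | 3.2% |
| 5% | 3.6 | 9.8 | 8.6% |
| 10% | 7.2 | 17.6 | 30.4% |

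For u = 10%: d = 0.0162 + 0.0036 + 0.0001 = 0.0199, and 1 − 0.9801¹⁸ = 0.304. The third column includes a few patients who are back at 50:50 after two opposite-arm reveals: 72(1 − u) × 3u²(1 − u) × 2/3 = 144u²(1 − u)², which is 0.01 at 1%, 0.3 at 5% and 1.2 at 10%.

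**Step 3: who can still be affected on the primary outcome.** Recruitment runs from December 2025 to October 2026, about 335 days. With 36 patients per centre (equal split assumed), that is one per centre every 335/36 ≈ 9 days, while END is read within 7 days of onset. Block-mates who enrolled earlier will mostly have a complete primary outcome. Averaged over the four positions in a block, (3 + 2 + 1 + 0)/4 = 1.5 of the 3 block-mates enrol later. So roughly half of the third column, or less if the unblinding comes late, could matter for the primary outcome.

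**Step 4: what a change of block size buys.** With membership known, one reveal gives 2/3 for blocks of 4, 3/5 for 6 and 4/7 for 8. With boundaries unknown, the chance that the adjacent code is in the opposite arm is, by simulation, about 0.63 for fixed 4, 0.60 for a random mix of 4 and 6, and 0.58 for a mix of 4, 6 and 8.

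**Step 5: bowel symptoms as a cue (illustration only).** The article gives no diarrhoea rate. At 1:1, P(QHF given diarrhoea) = q/(q + p), with q and p the rates on QHF and placebo. Assumed pairs: 10% and 10% give 0.50 (no cue); 20% and 10% give 0.67; 30% and 10% give 0.75; 50% and 5% give 0.91.

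**The case against.** The strongest reply is that the sentence on others remaining blinded is procedural: other participants' codes stay unopened. On that reading there is no contradiction, and the word others might even mean other staff. This stands as far as it goes. The sentence is not false on its procedural reading; the point is that the design does not fully deliver what a reader would take from it.

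The article also does not say that pack numbers run in sequence order or that block boundaries are visible, and numbering detail may well sit in a fuller document. That also stands for the pack-number route. It does not remove the enrolment-order route, which needs only a known block size and allocation in list order.

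Unblinding should be rare under the stated conditions. This holds too, and it is why the low end of the range belongs beside the high end. Those conditions limit how often a reveal happens, not what each one discloses.

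Two stronger readings are tempting and are not supported.

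- A reader might infer that one unblinding gives away the block-mates' arms. It does not: a guess is still wrong one time in three. Nor is it right to multiply 4 to 7 unblinded patients (5% to 10% of 72) by three and report 12 to 21 exposed. That is an upper bound on an assumed rate, and it ignores overlap within blocks and outcomes already complete.
- A reader might infer that bowel effects will unmask the NIHSS raters and bias the result towards QHF. Shared visit days do not mean shared personnel. No section says that the raters collect or see adverse events, the article states that they are blinded, and it gives no diarrhoea rate. This is a risk, and the direction of any bias is not established.

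**Conclusion.** The point holds as a limited weakness in the randomisation method, and it merits a cheap improvement. The probabilities within a block are exact. The trial-wide counts rest on assumed unblinding rates and on sites being able to tell who shares a block. Any effect on the primary outcome further requires that the revealed arm reaches someone scoring the NIHSS while a block-mate's 7-day window is open. At 1% unblinding the consequence is close to nil. At 10% it is no longer trivial for a trial of 72 patients with a 2-point rater-scored endpoint. The gain from varying the block size alone is modest, which is why scrambled pack numbers belong with it.

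**What to change.** Under Randomization, allocation, and blinding:

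1. Replace the single block size of 4 with randomly varying block sizes within centre. The independent biostatistician holds the sizes and does not disclose them to sites.
2. Number the packs in a scrambled order relative to the allocation sequence, so that a pack number carries no information about block membership.
3. Reword the assurance to say that other participants' codes remain unopened.

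As a secondary precaution, state under Safety outcomes and Follow up procedures that at each shared visit the NIHSS is scored and signed before the adverse-event questions are asked.

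Cost: before enrolment (planned to begin in December 2025), the list is regenerated in the same software and the packs are relabelled. Balance within centre becomes slightly looser. The order of assessments costs nothing. The sample size and the analysis do not change.
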